## Abstract

**Background:**

Fatigue is a common and disabling symptom in multiple sclerosis (MS), quantifiable by patient reported outcome instruments such as the Fatigue Scale for Motor and Cognitive Functions (FSMC). The pathophysiology of fatigue remains poorly understood, and effective treatments are limited. Emerging evidence implicates disrupted excitation–inhibition balance in the premotor cortex as a potential culprit of fatigue in MS. Converging evidence now show that such network imbalance can be modulated with repetitive transcranial magnetic stimulation (TMS). The efficacy of premotor rTMS retuning excitation-inhibition balance, thus improving MS-related fatigue, has yet to be examined in a clinical trial.

**Methods:**

This randomized, double-blinded, sham-controlled, parallel-group trial investigates the efficacy of premotor TMS in treating fatigue in MS. Fifty-eight patients with MS will receive either active or sham TMS targeting the left dorsal premotor cortex (PMd). On five consecutive days, participants will undergo 30-min sessions using a novel low-frequency (0.72 Hz) paired-pulse repetitive TMS protocol with an interstimulus interval of 33 ms. The primary endpoint is the change in FSMC score 6 days post-intervention. Secondary outcomes include additional fatigue assessments and quantification of regional γ-aminobutyric acid (GABA) and glutamate concentrations of the targeted PMd, via ultra-high-field (7T) magnetic resonance spectroscopy. We hypothesize that active treatment will result in greater fatigue reduction than sham treatment and correlate positively with an increase in regional GABA in the stimulated premotor region. Exploratory endpoints include structural and functional connectivity changes assessed with 7T resonance imaging and motor cortical excitability changes measured with TMS.

**Discussion:**

This study will assess the feasibility and efficacy of a novel low-frequency paired-pulse TMS protocol for fatigue in MS. Repeated neurophysiological measurements of cortical excitation–inhibition balance will yield mechanistic insights and guide future repetitive TMS trials targeting MS-related fatigue.

**Clinical Trial Registration:**

http://www.clinicaltrials.gov, NCT06569550.

## Highlights

This trial tests premotor repetitive TMS to reduce fatigue in relapsing-remitting multiple sclerosis.58 patients get active or sham low-frequency paired-pulse repetitive TMS over five days.The primary outcome is a change in FSMC scores six days after treatment.7T MR spectroscopy and TMS measures will link fatigue relief to excitation–inhibition balance.

## Background and rationale

Multiple sclerosis (MS) is an immune mediated disease targeting the central nervous system (1), with increasing global prevalence and incidence (2). Fatigue is highly prevalent in MS, affecting up to 78–95% (3, 4) of patients and is among the most disabling MS symptoms (5, 6). In people with MS, fatigue is consistently associated with decreased employment status and lower quality of life (4, 7–9).

The pathophysiology of fatigue in MS remains incompletely understood and involves multiple mechanisms (10–12). One hypothesis is that fatigue arises from an imbalance between cortical excitation and inhibition (13). This theory is supported by neurophysiological studies using electroencephalography (EEG) (14), transcranial magnetic stimulation (TMS) (15–18), and functional magnetic resonance imaging (fMRI) (19–21). Notably, individuals with high trait fatigue exhibit task-related hyperactivation of the premotor cortex during a non-fatiguing grip force task (20). Those patients who were capable of further increasing premotor activity following a fatiguing motor task reported lower fatigue in daily life (21). These findings suggest that trait fatigue is associated with an inefficient allocation of premotor cortical resources. Specifically, the disrupted excitation-inhibition balance may result in premature or excessive premotor activation during routine motor tasks, limiting the capacity of the central motor system for further upregulation when demanded. It is worth noting, that the exact mechanism of this disrupted excitation-inhibition balance remains unclarified, as there are studies that show both increased activation and increased inhibition, depending on modality and experimental setup (22, 23).

Pharmacological treatments targeting fatigue in MS have shown limited clinical relevance in the majority of patients (24–26). Physical exercise, in contrast, consistently shows a clinically relevant and positive impact on MS-related fatigue (24, 27, 28). However, exercise-based interventions may not be feasible for all patients, particularly those with advanced disability. Emerging evidence suggests that the beneficial effects of exercise may be mediated, at least in part, by modulating excitability within motor-related networks (16, 29). Currently, no approved therapies specifically target the imbalance in inhibition and excitation within the premotor-motor network.

Repetitive Transcranial Magnetic Stimulation (rTMS) is a non-invasive neuromodulation technique capable of inducing both local and network-wide plasticity in the brain (30–32). Several studies have shown that rTMS targeting the premotor cortex can produce direct and lasting modulatory effects on motor cortical excitability in healthy individuals (33–36). These effects depend critically on the stimulation parameters, including pulse type (e.g., single vs. paired or burst) and temporal patterning (37–39). When applied to the left dorsal premotor cortex (PMd) at an inter-stimulus interval (ISI) of 33 ms, low-frequency (0.7 Hz) paired-pulse rTMS (pp-rTMS) suppresses resting activity in a bilateral premotor-motor cortical network (40). This acute suppressive effect supports the potential of low frequency paired-pulse rTMS as a targeted intervention for network-level excitation-inhibition imbalances, including for potential alleviation of MS-related fatigue.

Side effects of rTMS include mild and transient local discomfort, headaches, and pain at the stimulation site (41, 42). Serious adverse events, including seizures, are exceedingly rare, when appropriate screening and safety protocols are followed (43, 44).

Few studies have directly examined the efficacy of rTMS for treating fatigue in people with MS. To date, only one small, randomized trial (*n* = 11 per group) has specifically assessed rTMS as treatment of MS-related fatigue, targeting either the motor or prefrontal cortex using an H-coil (45). In that study, no significant difference between active and sham treatment were observed, and the primary focus was safety (45). While several studies have reported reductions in fatigue as a secondary outcome (46–49), trials with the primary aim of alleviating fatigue and investigating the underlying mechanisms hereof are missing.

### Choice of sham comparator

Given the absence of an established, efficacious rTMS-based protocol for fatigue in MS, we have adopted a sham-control design for the present trial. Although other non-invasive brain stimulation modalities, such as transcranial direct current stimulation (tDCS) have shown some positive effect on fatigue in persons with MS (50, 51), considerable methodological heterogeneity across tDCS studies precludes its use as a standardized or mechanistically appropriate comparator. Therefore, a sham-controlled design offers the most rigorous and interpretable framework for evaluating the specific neuromodulatory effects of rTMS on fatigue and its neural correlates.

### Objectives

The primary objective of this study is to evaluate the effect of low-frequency paired-pulse rTMS on patient-reported fatigue in persons with MS. Participants will undergo a five-day intervention consisting of daily 30-min sessions of 0.7 Hz paired-pulse rTMS (inter-stimulus interval: 33 ms) targeting the left PMd. The primary hypothesis is that repeated paired-pulse rTMS of the left PMd will reduce fatigue severity, as measured by the change in Fatigue Scale for Motor and Cognitive Functions (FSMC) scores from baseline to 6 days post-intervention, relative to sham.

The secondary objective of this study is to determine whether changes in fatigue are associated with modulation of the excitation–inhibition balance within the motor and premotor cortex, as measured by ultra-high field 7 Tesla magnetic resonance spectroscopy (7T-MRS) assessed γ-aminobutyric acid (GABA) and glutamate (Glu) concentrations. The secondary hypothesis is that repeated paired-pulse rTMS targeting the left PMd will shift the balance toward relatively increased inhibition, and that the magnitude of this shift toward inhibition will correlate with the degree of individual fatigue reduction.

As an exploratory objective, we will investigate whether changes in fatigue, and its potential alleviation, are reflected in alterations in resting-state functional MRI (rs-fMRI) network dynamics. Additional exploratory outcomes include changes in clinical and behavioral measures related to fatigue.

### Trial design

This is a single-center, parallel-group, two-arm, double-blinded, sham-controlled, randomized trial. Participants will be randomly assigned in a 1:1 ratio to either the active intervention or sham control group. The intervention group will receive five sessions of 30-min rTMS targeting the left PMd, across 5 consecutive days while the control group will receive a sham version of the same protocol.

## Methods: participants, interventions and outcomes

### Study setting

All study procedures take place at the Danish Research Centre for Magnetic Resonance (DRCMR) at Copenhagen University Hospital Amager and Hvidovre, Copenhagen, Denmark. Participants are recruited through the outpatient clinic at Danish Multiple Sclerosis Center, Copenhagen University Hospital - Rigshospitalet, Glostrup, in Copenhagen, Denmark, as well as via the Danish Multiple Sclerosis Society (Scleroseforeningen). Recruitment began in August 2024.

### Eligibility criteria

Inclusion criteria: Participants must meet the following criteria to be eligible for the study: (i) Diagnosis of relapsing–remitting or secondary progressive MS, according to the 2017 McDonald criteria (52), (ii) Presence of moderate to severe fatigue, defined as a Fatigue Scale for Motor and Cognitive Functions (FSMC) score ≥ 53, and (iii) Age between 18 and 65 years.

Exclusion criteria: Participants will be excluded if they meet any of the following conditions: (i) Clinical relapse, corticosteroid treatment, or changes in MS-related medication within 3 months prior to inclusion, (ii) Moderate to severe depression, defined as a Major Depression Inventory (MDI) score ≥ 26 (53, 54) or other severe psychiatric, neurological, or somatic comorbidities, (iii) EDSS score (55) above 6.5 that would limit feasibility of 7T MRI, (iv) Contraindications to 7T MRI (56) or TMS (42, 44) in agreement with current safety guidelines (including pregnancy), (v) intake of pharmaceutical agents that may interfere with the neuromodulatory effect of rTMS, including tricyclic antidepressants (TCAs), monoamine oxidase inhibitors (MAOIs), GABAergic agents (benzodiazepines and gabapentin) and central stimulants such as modafinil. For feasibility reasons selective serotonin reuptake inhibitors (SSRIs), serotonin-norepinephrine reuptake inhibitors (SNRIs) are allowed. Use of selective serotonin receptor agonists (e.g., triptans for migraine) are allowed up to 48 h prior to intervention.

### Intervention—rTMS

Participants will receive five sessions of pp-rTMS, delivered once daily on five consecutive days. Each of the 5 pp-rTMS sessions consists of pulse pairs separated by an ISI of 33 ms (equivalent to 30 Hz) repeated at 0.72 Hz, for a total of 1,300 stimulus pairs per session. Each session will last 29 min and 55 s. Intensity of pp-rTMS will be personalized and adjusted to 80% of the individual’s resting motor threshold (RMT). Stimulation intensity will not be adjusted for difference in scalp-cortex distance between M1 and PMd, due to the low average difference in scalp-cortex distance between these 2 areas (57), and secondarily because a prior study investigating this paradigm over PMd did not adjust intensity, while demonstrating a non-linear relationship between stimulation intensity (40). Individual RMT will be determined on the first intervention day by administering single-pulse TMS over the left primary motor hand area (58). Should the paired-pulse stimulation of left PMd at 80% of RMT produce visible muscle twitches in the right hand, intensity will be reduced until twitches are no longer elicited, to reduce potential participant discomfort during the intervention protocol.

Stimulation will be delivered using a B65-Cool-A/P coil connected to a MagPro XP Orange Edition stimulator (MagVenture, Farum, Denmark). The B65-Cool-A/P coil is a butterfly-shaped coil with active cooling which can be used for both active and placebo stimulation. The MagPro XP Orange Edition stimulator can deliver high-frequency biphasic stimuli trains (2–5 pulses) up to 1,000 Hz with minimal intensity drop-off. To mimic the cutaneous sensation associated with active TMS pulses and preserve blinding, all participants will receive low-intensity electrical stimulation to the forehead, as described in the section on blinding.

Frameless stereotaxy will enable personalized neuronavigated PMd stimulation. The TMS coil position will be continuously controlled with a Localite neuronavigation system based on individual T1-weighted MRI brain scans (Localite, Bonn, Germany). The position of the coil for the duration of the intervention will be ensured with a robotic arm (TMS Cobot, Axilum, Schiltigheim, France), which has been shown to be superior to a rigid coil-holder in maintaining electric field (e-field) at target site during a 30-min session (59).

The stimulation target, the left PMd, is defined in montreal neurological institute (MNI) space (60) at x, y, z-coordinates (34, −2, 66), based on prior findings (21). This target is transformed into subject-specific space using individual T1-weighted and T2-weighted MRI brain scans. The optimal coil position will be calculated with SIMNIBS software (version 4.5^1^) as the scalp position inducing the largest mean electric field in the target region (61). Individual T1w and T2w MRI images will be segmented to a SIMNIBS compatible mesh using CHARM (62). The induced e-field for the B65-Cool coil (63) will be calculated (64, 65) in a 20 mm search radius at 1 mm resolution, with 40-50-degrees of rotation from the mid-sagittal plane, with an angular resolution of 1 degree.

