### Secondary outcome

#### 7 tesla proton magnetic resonance spectroscopy (^1^H-MRS)

The main secondary outcome is the between-group difference in changes in regional neurometabolite concentrations, specifically GABA and Glu, in the targeted left PMd, from baseline to the short-term follow-up on the final day of the intervention (Day 5). These concentrations will be assessed using ^1^H-MRS, acquired from a voxel positioned to cover the left PMd/M1 region. To assess neurometabolic network-level effects, an additional ^1^H-MRS voxel will be acquired in the contralateral (right) PMd/M1 region, to evaluate remote transhemispheric modulation. A voxel placed in the midline parietal region, will serve as a control site not expected to respond to the intervention. In addition to the short-term (Day 5) effects, longer-term effects will also be assessed at the primary follow-up 6 days post-intervention (Day 11), together with clinical outcome measures.

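### The left PMd target is printed with MNI x = +34, a right-hemisphere coordinate; the sign needs to be verified and corrected

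*Protocol article*

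**What the plan says.** The Protocol article gives one numeric definition of the stimulation target, in the section Intervention—rTMS: "The stimulation target, the left PMd, is defined in montreal neurological institute (MNI) space (60) at x, y, z-coordinates (34, −2, 66"), and attributes it to prior findings (reference 21). The same paragraph says how the figure is used: "This target is transformed into subject-specific space using individual T1-weighted and T2-weighted MRI brain scans". The coil position is then optimised for the mean electric field in the target region, within a 20 mm search radius.

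Elsewhere the target is consistently on the left:

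- Abstract, Methods: participants "will receive either active or sham TMS targeting the left dorsal premotor cortex (PMd").
- Trial design: "five sessions of 30-min rTMS targeting the left PMd, across 5 consecutive days".
- Intervention—rTMS, threshold: it is determined by "administering single-pulse TMS over the left primary motor hand area".
- Intervention—rTMS, intensity reduction: "Should the paired-pulse stimulation of left PMd at 80% of RMT produce visible muscle twitches in the right hand", the intensity is lowered.
- Secondary outcome (7T spectroscopy): the main comparison concerns "specifically GABA and Glu, in the targeted left PMd", and a further voxel "will be acquired in the contralateral (right) PMd/M1 region, to evaluate remote transhemispheric modulation".

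The Objectives and the Discussion also name the left PMd. The section Single-session outcomes of neurophysiology places the Day 1 excitability measures over the left motor cortex.

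**The concern.** The sign of x in an MNI coordinate identifies the hemisphere: negative is left, positive is right. The target sentence therefore gives two incompatible sides, one in words and one in the number, and the article offers no second coordinate or stated convention to settle which holds.

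This matters more than a slip in background text because a targeting pipeline takes a coordinate, not the word left. Anyone who reproduces the target from the number would plan the coil over the wrong hemisphere, although the wording beside it should alert a careful reader.

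A more serious consequence is conditional. If +34 had been entered in this trial, stimulation would have fallen on the side that the spectroscopy section treats as remote. The motor threshold, the Day 1 excitability measures and the main spectroscopy voxel would then all sit in the hemisphere opposite to the one stimulated.

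**Working it through.** **Inputs**

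- Printed target: (x, y, z) = (34, −2, 66), labelled left PMd (Intervention—rTMS).
- Search radius for the coil position: 20 mm (same section).
- Axis convention: x > 0 is right of the midline and x < 0 is left. This is the standard definition of the MNI space that the article names; the article states no departure from it.

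The printed coordinate cannot be reproduced from its source, because the cited prior study is not at hand. What can be checked is whether it agrees with the rest of the article.

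**Step 1: side implied by the number.** x = +34 lies 34 mm to the right of the midline.

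**Step 2: side implied by the text.**

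| Place in the article | Side implied for the target |
|---|---|
| Abstract; Objectives; Trial design; Discussion | Left, by name |
| Intervention—rTMS, threshold | Left motor hand area |
| Intervention—rTMS, twitch rule | Right hand, hence left hemisphere |
| Secondary outcome, main voxel | Left, by name |
| Secondary outcome, second voxel | Right is called contralateral, so the target is left |
| Single-session outcomes of neurophysiology | Left motor cortex |
| Intervention—rTMS, x coordinate | **Right** |

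Only the coordinate disagrees.

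**Step 3: size of the discrepancy.** If only the sign is wrong, the intended point is (−34, −2, 66). The distance between the two points is

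√[(34 − (−34))² + (−2 − (−2))² + (66 − 66)²] = √(68²) = 68 mm.

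Against the search radius: 68 / 20 = 3.4. A search centred on the printed point would not reach the left-sided one. The 68 mm is measured in template space; the distance in an individual head will differ somewhat, but not enough to change that conclusion.

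**Step 4: could the sign have been lost when the PDF was read?** The minus sign on y = −2 in the same triplet is intact. Loss of the sign on x alone is therefore unlikely, though it cannot be fully excluded without the typeset page.

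**Step 5: possible causes.** A dropped minus sign is the likeliest. A right-hemisphere peak taken from the prior study and not mirrored to the left is also possible. The article cannot separate the two, nor can it confirm that 34 is the right magnitude.

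**The case against.** The strongest reply is that this is a typographical slip with no bearing on the trial. The intended side is in no doubt, since the word left stands in the same sentence as the number. The procedures also make an unnoticed wrong-side treatment improbable. The threshold is found over the left motor cortex and the right hand is watched. The coil is navigated on each participant's own scan and held by a robotic arm. At least two trained staff attend every session, and a dedicated TMS researcher attends Day 1. No outcome, sample size or analysis depends on the printed sign. The full protocol may carry the correct value, and a review of navigation records goes further than a suspected misprint requires.

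Much of this stands. The safeguards make wrong-side stimulation unlikely, and the 68 mm matters for treatment only if +34 was really used. The statement that this is the sole numeric target definition applies to the article; the full protocol and the supplement were not available.

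Two things do not fall away. The safeguards do not correct a published coordinate that contradicts its own sentence. Nor do they show which sign the targeting script holds. That an article condenses a longer protocol excuses omissions, but this is a stated figure. Looking up the planned coil side in records that already exist is a small task, and it settles the one branch that would be serious.

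**Conclusion.** The concern holds. The article's numeric target lies in the right hemisphere, while its wording and every linked procedure place the target on the left. The discrepancy is 68 mm in MNI space, on the assumption that the magnitude 34 is correct and only the sign is wrong. The conclusion rests on the standard MNI axis convention, from which the article declares no departure.

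What is certain is a wrong or ambiguous target definition in print. Wrong-side treatment is only a possibility, nothing in the article indicates that it happened, and under a pure misprint no participant is affected. The point should be fixed because the coordinate is an operative input to the intervention and is cheap to verify. It does not call the trial's design or analysis into question.

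**What to change.** 1. Read the x value in the targeting script and compare it with the source study.
2. For participants already treated (recruitment began in August 2024, section Study setting), confirm from the neuronavigation records that the planned coil position was on the left.
3. Until unblinding, check the side only. Leave the delivered-field simulations described under Simulated E-fields closed: the sham side of the coil is meant to deliver no effective field, so those results could differ by arm. The article does not say how the simulations treat the sham arm, so this is a precaution.
4. Print the verified coordinate, expected to be (−34, −2, 66). If a different axis convention was used, state it instead.
5. Report any participant found to have been treated on the right.

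The cost is one corrected figure and a short check of existing files. No new data are needed, and the sample size, outcomes, randomisation and analysis stay as they are.

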### Intervention—sham rTMS

Participants in the sham group will receive the same low-frequency pp-rTMS protocol as the active group. However, the stimulation coil will be flipped, with the placebo side facing the scalp. This orientation, achieved by rotating the coil along its longitudinal axis, prevents the delivery of a biologically effective magnetic field while preserving the auditory and tactile experience of stimulation. As with the active group, concurrent low-intensity electrical stimulation will be applied near the stimulation site to mimic cutaneous sensations. While this approach reflects current best practice in the field it is worth noting that transcutaneous stimulation may by itself be As recently shown, sham rTMS by transcutaneous electrical stimulation may by itself be considered an active control, rather than an inert control (66).

